#### Estimation of sample size

Sample size will be optimized to achieve sufficient power for hypothesis testing. Assuming an error probability of α = 0.05, test power of 1−β = 0.95, a large effect of time with *f* = 0.40, and a repeated measures correlation of *r* = 0.1, we computed minimum sample sizes of *N* = 40 analyzed adolescents and *N* = 40 analyzed personnel with the G*Power software (64). Large effect sizes were anticipated given that the actual intervention effect size (15) had not yet been analyzed at the time of the inception of DELTA-JU and the proposal for funding and ethics approval in 2020.

Considering the dropout rates from BL to FU for adolescents (assuming 20%) and personnel (assuming 10%), at least *N* = 50 adolescents and *N* = 45 personnel will have to be included at BL. In case that dropout rates exceed 20%, we will continue to sample participants in order to achieve the required analysis sample size of *N* = 40 nonetheless as long as study funding is available. For qualitative interviews, a sample size of *N* = 10 was deemed as an adequate compromise between resources and expected output.

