#### Hypotheses

Aim (A) is reached when for each need, identified through qualitative analyses of interviews, one or more adjustments to the content or procedure of DELTA-JU is documented. No quantitative hypothesis is applicable. Aims (B) and (C) are achieved through testing the following hypotheses in adolescents who are abstinent for alcohol and drugs except nicotine/tobacco:
Adolescents: relevant increase in SUD-related subjective utility through FU (descriptive: a medium rating of 2.0 or higher in the respective GEJ items across participants);Adolescents: significant reduction of substance-related craving as a measure of relapse risk (*p* < 0.05, MaCS score) through FU;Adolescents: significant reduction of SUD severity (*p* < 0.05, scores of FTND, AUDIT, and DUDIT) through FU;Adolescents: significant reduction of self-reported past-month tobacco use through FU (*p* < 0.05, substance use interview);Personnel: relevant increase in SUD-related subjective utility through FU (descriptive: a medium rating of 2.0 or higher in the respective GEB items across participating personnel); andPersonnel: high satisfaction ratings concerning the workshop organization (descriptive: a medium rating of 4.0 or higher in the respective GEB items across participating personnel).

Additionally, secondary outcomes in adolescents (BDI-II, PQ-16, UCLA-PTSD, PSS-10, and SWLS) and personnel (ERI-S-10) will be tested exploratorily for changes through FU as previously done in the DELTA evaluation (15). All reductions through FU in adolescents are expected to be descriptively larger than reductions over the natural course, i.e., from PRE to BL in the WL group.

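### The 95% power given for 40 personnel applies to no personnel primary outcome, because both are judged by descriptive cut-offs

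*Protocol article*

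**What the plan says.** Estimation of sample size gives the purpose of the calculation: "Sample size will be optimized to achieve sufficient power for hypothesis testing". One set of inputs serves both samples. The significance level is 0.05 and the target power is 95%. The effect to be detected is "a large effect of time with *f* = 0.40", and scores on the two occasions are taken to correlate at 0.1. The result is 40 analysed adolescents and 40 "analyzed personnel with the G*Power software". The personnel figure is then raised to 45 for an assumed dropout of 10%.

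Quantitative measurements names GEB-K (subjective utility) and GEB-S (satisfaction with the workshop) as the personnel primary outcomes. Hypotheses sets their criteria. Hypothesis 5 needs a GEB rating of at least 2.0 and is marked descriptive. Hypothesis 6 reads "high satisfaction ratings concerning the workshop organization (descriptive: a medium rating of 4.0 or higher in the respective GEB items across participating personnel". Neither carries a p-value, whereas hypotheses 2, 3 and 4 each carry p < 0.05.

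Data analysis applies the repeated-measures MANOVA to the non-descriptive hypotheses, which it lists as 2–4. All three concern adolescents. Hypotheses adds that ERI-S-10, a personnel measure of work stress, will be tested for change on an exploratory basis. Table 3 has ERI-S-10 at baseline and follow-up.

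**The concern.** A power figure belongs to a particular test: it needs a null hypothesis, an error rate and an effect on the scale being tested. The calculation describes a within-person comparison of two occasions. Hypotheses 5 and 6 compare an average rating with a fixed value, without a null hypothesis, an α or a correlation between occasions. The personnel sample is thus justified by a property that the personnel primary analysis does not have.

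Aim B (acceptability) depends, on the personnel side, on these two cut-offs. Someone who reads only the sample size section could credit those conclusions with 95% power. The quantity that bears on them is how precisely 40 people estimate a mean rating, and the article does not give it.

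**Working it through.** **Step 1. Reproduce the stated figure.** Inputs from Estimation of sample size: α = 0.05, power 0.95, f = 0.40, r = 0.1. The number of occasions is taken as m = 2 (baseline and follow-up, as in Data analysis), with one group. For a within-subject F test:

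- noncentrality λ = f² × N × m / (1 − r), with m − 1 and (N − 1)(m − 1) degrees of freedom
- at N = 40: λ = 0.16 × 40 × 2 / 0.9 = 14.2 on 1 and 39 df, power 0.957
- at N = 39: power 0.952
- at N = 38: power 0.947

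The minimum is 39, and the stated 40 meets the target. The dropout step also agrees: 40 / (1 − 0.10) = 44.4, rounded up to 45.

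**Step 2. Identify the test that this describes.** With two occasions the same inputs correspond to a paired standardised difference of 2f / √(2(1 − r)) = 0.80 / √1.8 = 0.60. The calculation is for a mean change within persons.

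**Step 3. Match it to the personnel outcomes.**

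| Personnel outcome | Status | How it is judged | Test of change planned? |
|---|---|---|---|
| GEB-K (hypothesis 5) | primary | rating of at least 2.0, descriptive | no |
| GEB-S (hypothesis 6) | primary | rating of at least 4.0, descriptive | no |
| ERI-S-10 | exploratory | change through follow-up | yes |

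Only the last row has the form of the powered test.

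**Step 4. Work out what 40 personnel give the primary outcomes.** For a mean of independent ratings, the 95% half-width is t(0.975; 39) × SD / √40 = 2.023 / 6.325 × SD = 0.32 SD.

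The article gives no SD for either GEB scale. If the SD of a person's mean rating is assumed to lie between 0.6 and 1.2 points, the half-width is 0.32 × 0.6 = 0.19 to 0.32 × 1.2 = 0.38 points. That range is an illustration, not a figure from the article. GEB-K is scored 0–4 and GEB-S 1–5.

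**The case against.** The strongest reply is that nobody need be misled. The word descriptive stands inside both personnel hypotheses, Data analysis leaves them out of the MANOVA, and the sample size section speaks of hypothesis testing in general, not of primary outcomes. A personnel test of the powered form does exist, for ERI-S-10. No N, decision rule or error rate would change. This stands, and it keeps the severity low. It does not remove the mismatch: the section assigns the power calculation to the personnel sample without saying that it leaves out the personnel primary outcomes, and it never names ERI-S-10 as its basis. Nor is this a detail left to an analysis plan, since the article makes the statement itself.

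Three stronger readings are tempting, and the article does not support them.

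- **The power belongs to no primary test at all.** Adolescent hypotheses 2–4 are primary and are tested as change from baseline to follow-up. The finding concerns personnel only.
- **The personnel primary outcomes are rated only once, so no time effect could exist.** Table 3 shows GEB-S at follow-up only. Sampling stage, however, has personnel assessed on the workshop day and again 16 weeks later, with questionnaires on workshop content and organisation. The GEB-K row of Table 3 has empty cells where other rows have dashes, so little can rest on it. The two places need reconciling, but the finding does not depend on the answer: even with two ratings, no test of either scale is planned.
- **Clustering shrinks the sample to some definite effective size.** Staff attend shared workshops, so ratings may be correlated. The article gives neither the number of staff per workshop nor an intraclass correlation, so no definite figure follows.

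**Conclusion.** The point holds for personnel, and the sample size statement is wrong as written in that respect. The calculation is correct for a two-occasion change, but the personnel primary outcomes are not analysed as change, so the 95% power does not describe hypotheses 5 and 6. At most it describes the exploratory ERI-S-10 change, and then only under the assumed f = 0.40, which the article does not support for that scale specifically.

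For the primary ratings, 40 personnel give a 95% interval of about ±0.32 SD. This assumes independent ratings and 40 analysed people. Correlation within workshops or institutions would widen it by an amount that the article does not allow one to calculate. Severity is low: the descriptive status is openly declared, and neither the sample nor the data collection is affected.

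**What to change.** 1. In Estimation of sample size, state that the power calculation does not apply to hypotheses 5 and 6 and that, for personnel, it refers at most to the exploratory ERI-S-10 change under the assumed f = 0.40.
2. Justify the personnel N by precision. Suggested wording: *For the personnel ratings, 40 analysed participants give a 95% confidence interval of about ±0.32 SD around a mean, if ratings are independent; the interval will be wider if ratings cluster by workshop or institution.*
3. Report the 95% confidence interval beside the 2.0 and 4.0 cut-offs, so that a reader can see whether each is clearly met.
4. Separately, reconcile Sampling stage (personnel assessed twice) with Table 3 (GEB-S at follow-up only), and say which occasion supplies the rating for each cut-off.

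The cost is wording and one extra reported interval per scale. The 40 analysed and 45 included personnel stay as they are, and no data collection is added unless step 4 shows that Table 3 omits a planned rating.

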#### Setting and participants

Youth welfare institutions will be approached if they are in the study region (district of Saxony and, if feasible, surrounding areas in Brandenburg and Thuringia). Generally, those institutions specialized in SUD care are placed outside of metropolitan areas (32) in order to reduce risk factors for relapse (such as contact to drug dealers) (33). Adolescents and their legal guardians will be approached by personnel of participating institutions. If interested, study personnel will hand out information material and will answer all questions in person, via telephone or via e-mail. Consent will be given after additional verbal information to adolescents. Inclusion criteria for adolescents are: (1) aged 12.00–17.99 years, (2) SUD diagnosis, or (3) chronic substance use during the past. The only exclusion criterion is low cognitive functioning (intelligence quotient <70). For BL-FU analyses, we will not analyze participants who did not attend any of the 16 sessions for whatever reason or if study participation was discontinued due to an adverse event. Participants choosing to discontinue are immediately asked whether they want to provide data on primary outcomes anyhow. Personnel of youth welfare institutions is included if they work with at least 20 h/week in a cooperating institution. The anticipated flow of adolescent participants is shown in Figure 2. At the time of writing this protocol, study registration is completed (01. Feb 2022) and the first adolescent participants are being recruited, randomized, and enrolled (starting 02. Feb 2022).

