### Strengths and limitations

The presented study design has several strengths. First, it is in line with ethical requirements that all adolescents are offered treatment. Waiting for 16 weeks in the WL condition still seems adequate given that adolescents may reside for up to 2 years in youth welfare institutions. In randomized clinical trials, for example, only cases may have received treatments. Second, it requires a smaller sample when participants become part of several analysis groups (intervention vs. WL). Third, alternative explanations of time effects may be controlled for by comparing BL-FU effects with PRE-BL effects.

Challenges arise from uncontrolled parallel treatments during the waiting period. Such treatments cannot be included in the quantitative estimation of treatment effects due to the limited number of participants in each group. Furthermore, homogeneity of cooperating youth welfare institutions is limited. Results may thus have to be replicated in other and diverging institutions. Although the sample size was *a-priori* calculated to maximize the use of available resources, drop-out rates may be unexpectedly high. In this case, additional participants and institutions may have to be recruited. In case of limited sample size, using Bayesan methods instead of testing for differences from zero may be advisable (74). Both the AUDIT and DUDIT have been previously used to assess changes in alcohol- and drug-related problems in adolescents and young adults using 3-month intervals between BL and FU (75, 76). Nevertheless, it remains possible that small changes in problems might go unnoticed given that both instruments cover 12 month periods. Another limitation arising from the limited sample size in a phase II study is the impossibility to adjust for several baseline variables. Such superior analysis strategies are not feasible at this point of the intervention development but will be imperative during phases III/RCT and phase IV studies in the future. The same holds true for the analysis of relevant patient subgroups (e.g., differentiating those with primarily alcohol-related problems from those with primarily cannabis-related problems) and intention-to-treat analyses or sensitivity analysis. Finally, additional measures that would objectify relapse to the use of alcohol or other drugs were not funded and will have to be implemented in a future trial, preferably a multi-center RCT testing DELTA-JU against treatment-as-usual.

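### The before-after test uses only adolescents with both baseline and follow-up values, and a small sample is not a valid reason to rule out intention-to-treat and sensitivity analyses

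*Protocol article*

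**What the plan says.** All references are to the protocol article.

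- **Data analysis.** The test is a repeated-measures MANOVA with time (BL, FU) as the factor. It is run in 40 adolescents and requires at least one session attended. A significant reduction over time is read as a relevant intervention effect, and between-group effects are called unimportant.
- **Estimation of sample size.** The required number is 40 analysed. "Considering the dropout rates from BL to FU for adolescents (assuming 20%) and personnel (assuming 10%), at least" 50 adolescents and 45 personnel are to be included at BL. For adolescent dropout above the assumed rate, the text goes on: "we will continue to sample participants in order to achieve the required analysis sample size of" 40, as long as there is funding.
- **Data management.** Missing items are replaced by the questionnaire mean when at least 80% were answered. No rule is given for an FU that is missing altogether.
- **Strengths and limitations.** Adjustment for baseline variables is called impossible because of the limited sample. The same is said to hold for subgroup analyses "and intention-to-treat analyses or sensitivity analysis", all of which are left to later phases.
- **Setting and participants.** Adolescents discontinued because of an adverse event are left out of the BL-FU analysis. For the others: "Participants choosing to discontinue are immediately asked whether they want to provide data on primary outcomes anyhow". Nothing says at what date these data are taken or whether they enter the test.

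**The concern.** The reason given for ruling out these analyses fits the other items in the same list. Covariate adjustment and subgroup analysis do burden or divide a small sample. An analysis of all starters does the opposite, because it adds adolescents.

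The point matters because the claim of effect is a within-person change. If adolescents who do worse are more often missing at FU, the mean change in those who remain is too favourable. The only planned comparison, PRE to BL in the waitlist group, is descriptive and covers a period before treatment, so it does not correct for loss during treatment. Recruiting further adolescents brings the number with FU back to 40, which restores precision. It does not make those 40 representative of everyone who started.

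**Working it through.** **1. The plan's own figures.** The inputs come from Estimation of sample size. The error rates are given as "Assuming an error probability of α = 0.05, test power of 1−β = 0.95". The effect size is f = 0.40 for change over the two time points, and the assumed correlation between them is 0.1 (r below). For one within factor with m = 2 time points:

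- noncentrality λ = f² × N × m / (1 − r), with 1 and N − 1 degrees of freedom
- N = 40: λ = 0.16 × 40 × 2 / 0.9 = 14.22, power 0.957
- N = 39: power 0.952; N = 38: power 0.947

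The smallest sufficient N is 39, so the stated 40 is sound. The inflation for dropout is also right: 40 / 0.8 = 50 and 40 / 0.9 = 44.4, rounded up to 45. The step from 50 to 40 shows that the plan counts dropouts as lost to the analysis.

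**2. How many starters stand behind 40 analysed.** Starters = 40 / (1 − p):

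| Dropout p | Starters | Not analysed |
|---|---|---|
| 20% | 50 | 10 |
| 30% | 58 | 18 |
| 40% | 67 | 27 |

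The analysed number stays at 40 while the unanalysed share grows.

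**3. Does a small sample argue against analysing all starters?** If all 50 had an FU, power at f = 0.40 would be 0.985. That is an upper bound, because leavers without FU add only their BL value. Now suppose instead that leavers have no FU and are counted as unchanged, while those who stay improve by 0.80 SD (f = 0.40 with two time points; variance of change 2 × (1 − 0.1) = 1.8). At 20% dropout:

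- mean change = 0.8 × 0.80 = 0.64 SD
- variance of change = 0.8 × 1.8 + 0.2 × 0.8 × 0.64 = 1.542
- λ = 50 × 0.64² / 1.542 = 13.28, power 0.946

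At 30% (58 starters) and 40% (67 starters) the power is 0.944 and 0.936. Power is therefore no obstacle.

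**4. Size of the overstatement.** This is an assumption, not a figure from the documents. If leavers do not change, the effect in those with FU divided by the effect in all starters is 1 / (1 − p): 1.25 at 20% and 1.43 at 30%. If leavers worsen by 0.4 SD, the all-starters change falls from 0.80 to 0.8 × 0.80 − 0.2 × 0.4 = 0.56 SD at 20%, and to 0.7 × 0.80 − 0.3 × 0.4 = 0.44 SD at 30%.

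**5. What each analysis does to false-positive findings.** Simulation with true mean change zero, one outcome, 40 adolescents with FU, and a test in the direction of benefit (nominal 0.025). The correlation of 0.3 or 0.5 between leaving and poorer change is assumed.

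| Analysis | 20% dropout | 30% dropout |
|---|---|---|
| Pairs only, correlation 0.3 | about 0.10 | about 0.15 |
| Pairs only, correlation 0.5 | about 0.20 | about 0.38 |
| Leavers set to no change, correlation 0.5 | about 0.20 | about 0.37 |
| Likelihood model on all values, correlation 0.5 | about 0.10 to 0.15 | about 0.16 to 0.26 |

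The ranges in the last row run from a BL-FU correlation of 0.1 (the protocol's value) to 0.5 (assumed). The model on all available values reduces the error but does not remove it. Counting leavers as unchanged shrinks the mean and its standard error together, so it corrects the estimate and not the significance verdict.

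**The case against.** The strongest reply is that this is an openly exploratory phase 2 trial that discloses the limitation, records dropout and discharge (Additional measures), reviews missing-data patterns twice a year (Data management) and asks discontinuers for primary outcomes. All of that is true, and it softens the point. It does not repair the stated reason, and no rule brings the discontinuers' data into the test.

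A second reply is that the proposed analyses do not cure outcome-related loss. Step 5 confirms this, so they should be presented as a reduction of bias and as an estimate of its size.

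A reader might also infer four stronger things that the documents do not support.

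- **That topping up causes the bias.** It applies only above 20% dropout and while funding lasts. The selection would be the same if recruitment stopped at 50.
- **That the rule on missed sessions and positive urine tests shows that leavers do worse.** That rule stands under DELTA intervention before revision. It is a temporary exclusion from group sessions with re-entry possible, and it is not loss to FU.
- **That discontinuers are assessed at the wrong time.** The word on immediacy governs when they are asked, not clearly when they are measured. Sampling stage places FU 16 weeks after the first session.
- **That only full attenders are analysed.** One session plus BL and FU is enough.

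The simulated rates are for a single outcome, not for the planned omnibus test over five, and they rest on assumed correlations.

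**Conclusion.** The concern holds as a correction to the analysis plan. The decisive test is restricted to adolescents with both values, and the analyses that would show the effect of this restriction are ruled out for a reason that does not apply to them. The sample-size figures themselves are correct.

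The direction of bias is favourable if leaving goes with poorer outcome, which the documents neither establish nor exclude. Its size cannot be derived from them. The factors 1.25 and 1.43 rest on the assumption that leavers do not change, and the false-positive rates on assumed correlations of 0.3 to 0.5.

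**What to change.** 1. In Strengths and limitations, delete the statement that intention-to-treat and sensitivity analyses are not feasible.
2. In Data analysis, add a mixed model on all available values (available in SPSS) for every adolescent who started and has a BL, with later recruits added to the leavers. State that this reduces bias but does not remove it if leaving depends on the unseen outcome.
3. Report the mean change with leavers without FU counted as unchanged, and ideally also with leavers counted as worse. Label these as sensitivity estimates of effect size, not as a safeguard for significance.
4. In Setting and participants, state that discontinuers' primary outcomes are sought at the scheduled FU, 16 weeks after the first session, and enter the analysis.

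The cost is one additional model, one contact at a date already scheduled, and a possibly less favourable estimate. No extra adolescents are needed.

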## Discussion

The DELTA-JU study will create a setting-specific manual for highly vulnerable adolescents who suffer from one or more SUDs, and, in many cases, from co-occurring mental disorders. We believe that DELTA-JU will be (a) properly adjusted to setting-specific needs of youth welfare institutions offering housing for adolescents with SUD, (b) accepted both by adolescents and the institutions’ personnel, and (c) effective in remaining abstinent from substances, reducing tobacco smoking, and reducing SUD problems. Providing feasible and effective treatments that are accepted by their respective target population is one primary goal set both for mental health research and practice in Europe (65).

As in all interventions, an age-specific approach is warranted when approaching children and adolescents. DELTA and DELTA-JU indeed provide an age-adequate intervention that includes material, methods, and content created for adolescents’ needs specifically while avoiding topics and approaches better suited for adults or older adults, e.g. (66). Furthermore, DELTA and DELTA-JU integrate modules on prevalent and outcome-relevant problems besides SUD, i.e., for depressiveness, for emotion regulation, and coping with stress and boredom. Addressing such co-occurring psychopathologies is in line with current recommendations for state-of-the art psychotherapeutic treatments (67). In the future, psychotherapeutic interventions such as DELTA-JU may be accompanied by including virtual reality elements or mobile phone-based elements.

Giving that effects can be independently replicated, it can be disseminated within other institutions of youth welfare. This will help institutions to professionalize their service for adolescents with SUD and it provides another currently lacking tool (68) for the outpatient treatment of SUDs before and after inpatient detoxification treatment (69). At the same time, we believe that besides treatment for diagnosed SUDs, efforts in prevention and early intervention are necessary nonetheless (70).

From a long-term perspective, programs such as DELTA-JU may help to alleviate the immense societal costs relating to consequences of alcohol use (27pprox. 32.5 billion EUR per year in Germany) (71), tobacco use (97.2 billion EUR) (72), cannabis use (0.9 billion EUR) (73), and the use of further substances for which no estimations are available.

